**Study Sessions and Exercise Protocol**

The trial will comprise four sessions with seven-day washouts. Procedures will remain identical except for the randomized intervention applied. Assessments will occur before and after each WOD.

- Exercise Protocol – WOD: To minimize circadian and external influences, participants will perform the WOD at the same time in all sessions and will avoid physical activity from 24 h pre-WOD to 48 h post-WOD. The WOD will follow the Cross Training 21-15-9 scheme (three rounds, no rest), aiming for the fastest possible completion. Repetitions will be monitored by an independent assessor.

The exercises will include:

1. Assault AirBike Calories: Participants will use a standardized AirBike model, pedaling until they reach the target calorie count required for each round.
2. Hang Squat Clean: The exercise will start with the participant holding the barbell in the hang position (above the knees) with arms fully extended. From this position, the barbell will be cleaned to the shoulders while the hips descend below the knees. A repetition will be validated when full hip and knee extension is achieved with the bar resting on the shoulders.
3. Box Jump Over: Participants will perform a two-foot jump onto a 60.69-cm (24-inch) box, ensuring both feet contact the top surface before jumping down to the opposite side.

**Outcomes**

The primary outcome will be the change in performance on the functional test, assessed 1-hour post-WOD. Secondary outcomes will include: change in functional test performance at 24 and 48 hours post-WOD; biochemical markers of muscle damage and oxidative stress; antioxidant activity; subjective perception of exertion (assessed at 1, 24, and 48 hours post-WOD); and satisfaction with the intervention (assessed at 48 hours post-WOD).

- Vertical Jump Performance: Vertical jump performance will be measured using the countermovement jump (CMJ) height test (Balsalobre-Fernández et al., 2015). During the test, participants will stand with feet shoulder-width apart and hands on the hips. They will perform a controlled squat to ~90° of knee flexion followed by an explosive vertical jump. Upon landing, they will flex the hips, knees, and ankles to absorb impact. A smartphone camera, positioned 1.5 m away, will record three maximal-effort CMJ attempts (Balsalobre-Fernández et al., 2015). Jump height will be analyzed using the JumPo 2 app (iOS), the only validated tool available at the time. The highest recorded jump will be used for analysis.
- Muscle Damage and Oxidative Stress Markers: Muscle damage will be assessed via lactate dehydrogenase (LDH) levels (De Oliveira et al., 2017). Oxidative stress and antioxidant activity will be assessed using thiobarbituric acid reactive substances (TBARS), carbonylated proteins, catalase (CAT), and superoxide dismutase (SOD) (Pinto et al., 2022). Blood samples (5 mL) will be drawn from the anterior cubital vein and stored at −80 °C for later analysis. LDH activity will be quantified by spectrophotometry using specific reagent kits (Labtest®, Minas Gerais, Brazil) as an indirect marker of muscle damage. TBARS, carbonylated proteins, CAT, and SOD will be analyzed as biomarkers of oxidative stress and antioxidant defense following previously established spectrophotometric protocols (Pinto et al., 2022). Each biochemical analysis will be conducted in triplicate, and the mean value will be used for statistical interpretation.
- Subjective Perception of Exertion: Perceived exertion will be assessed using the Rate of Perceived Exertion (RPE) scale (Fanchini et al., Weston et al., 2015). Participants will rate effort in two domains:
- RPE-MI (Muscular Intensity): perceived lower-limb fatigue.
- RPE-R (Respiratory Effort): perceived cardiorespiratory fatigue.
  Volunteers will complete two identical RPE scales ranging from 0 to 100, corresponding to muscular and cardiorespiratory effort.
- Satisfaction with the Intervention: Satisfaction will be assessed 48 hours post-WOD using a 5-point Likert scale: (1) Very unsatisfied, (2) Unsatisfied, (3) Neutral, (4) Satisfied, (5) Very satisfied. For analysis, responses will be dichotomized as satisfied (“satisfied” and “very satisfied”) versus not satisfied (“neutral,” “unsatisfied,” and “very unsatisfied”).

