**Blinding and Randomization**

Outcomes will be assessed by an independent evaluator who will be blinded to group allocation. Intervention sequences will be randomized (1:1:1:1) via www.randomization.org by a researcher not involved in other phases of the study. Each participant will complete all four interventions across weekly sessions with seven-day washout periods. Allocation will be concealed using sealed, numbered, opaque envelopes.

The intervention orders will be:

- Sequence 1: PR → PBMT-sMF → ESWT → IPC
- Sequence 2: PBMT-sMF → ESWT → IPC → PR
- Sequence 3: ESWT → IPC → PR → PBMT-sMF
- Sequence 4: IPC → PR → PBMT-sMF → ESWT

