**Statistical Analysis**

To the best of our knowledge, no prior study will have compared PBMT-sMF, IPC, ESWT, and passive recovery in Cross Training athletes. Therefore, sample size will be calculated based on CMJ performance data from the first session, following a previously described method (Pinto et al., 2022). This calculation will be conducted by a blinded researcher and will use percentage changes in CMJ at 1-hour post-WOD (primary outcome). An 80% statistical power (α = 0.05; ANOVA) will be considered, and the WebPower (https://webpower.psychstat.org/models/means03/effectsize.php) and Statistics Kingdom (https://www.statskingdom.com/sample_size_regression.html) tools will be used for the computation.

Statistical analyses will follow the intention-to-treat principle (Elkins, 2015). The statistician will remain blinded to allocation to minimize bias. Data normality will be assessed using the Shapiro–Wilk test. Differences between interventions will be evaluated using repeated-measures ANOVA with Bonferroni post hoc tests. Both absolute values and percentage changes from baseline will be analyzed. Results will be presented as mean ± SD (tables) and mean ± SEM (figures). Fisher’s exact test will be used to compare satisfaction proportions across interventions. Statistical significance will be set at p < 0.05.

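### Satisfaction is collected on five ordered levels but analysed only as satisfied versus not, which costs power and hides any difference lying on one side of the cut

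*Protocol*

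**What the plan says.** In the protocol's Outcomes section, satisfaction closes the list of secondary outcomes: "and satisfaction with the intervention (assessed at 48 hours post-WOD"). The scale is ordered: "Satisfaction will be assessed 48 hours post-WOD using a 5-point Likert scale", running from very unsatisfied (1) to very satisfied (5). The form of analysis is then fixed: "For analysis, responses will be dichotomized as satisfied" (levels 4 and 5) "versus not satisfied (“neutral,” “unsatisfied,” and “very unsatisfied" (levels 3, 2 and 1).

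The Statistical Analysis section says that Fisher's "exact test will be used to compare satisfaction proportions across interventions". It describes no analysis of the five levels as such. The design is a crossover (Blinding and Randomization): "Each participant will complete all four interventions across weekly sessions with seven-day washout periods". Each athlete who completes the trial therefore gives four ratings.

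On the error rate, "Statistical significance will be set at p < 0.05". Power is planned for the countermovement jump alone: "An 80% statistical power (α = 0.05; ANOVA) will be considered", using the percentage change at 1 hour. No sample size is given, because it is to be derived from first-session jump data. No satisfaction rate or rating distribution is assumed anywhere.

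**The concern.** The trial compares four options that each athlete experiences in turn. For satisfaction, the useful signal is whether an athlete rates one option above another. The cut keeps that signal only when the two ratings fall on opposite sides of the line between levels 3 and 4. An athlete who answers *satisfied* for one device and *very satisfied* for another becomes a tie, as does one who answers *very unsatisfied* and *neutral*. No test applied after the cut can recover such a preference.

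What is at stake is the chance of detecting a real difference in satisfaction, and the risk of reporting no difference when the levels already collected would have shown one. The protocol states this choice outright, so it is not a detail left to a statistical analysis plan.

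**Working it through.** The protocol states no sample size, power or expected rate for satisfaction, so there is no figure to reproduce. From the protocol come the five levels, the 4–5 versus 1–3 cut, the crossover and the 0.05 level. Two-sided testing, the rating distributions, the effect sizes, the correlation and the numbers of athletes are assumptions.

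**1. Efficiency lost by the cut.** Under proportional odds, the information in an ordered rating with level probabilities p₁…p₅ is proportional to 1 − Σpᵢ³. After the cut, with s = p₄ + p₅, it is proportional to 1 − s³ − (1 − s)³. Relative efficiency is the ratio of the second to the first.

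| Assumed distribution, levels 1–5 | s | Five levels | After cut | Ratio | Loss |
|---|---|---|---|---|---|
| .20/.20/.20/.20/.20 | 0.40 | 0.960 | 0.720 | 0.75 | 25% |
| .10/.20/.40/.20/.10 | 0.30 | 0.918 | 0.630 | 0.69 | 31% |
| .05/.10/.25/.35/.25 | 0.60 | 0.925 | 0.720 | 0.78 | 22% |
| .03/.07/.15/.40/.35 | 0.75 | 0.889 | 0.562 | 0.63 | 37% |
| .02/.03/.05/.40/.50 | 0.90 | 0.811 | 0.270 | 0.33 | 67% |

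For the first row, 1 − 5 × 0.2³ = 0.960 and 1 − 0.4³ − 0.6³ = 0.720, so the ratio is 0.75.

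**2. A difference on one side of the cut.** Suppose one intervention is rated .05/.05/.10/.60/.20 and another .05/.05/.10/.20/.60. The proportion satisfied is 0.60 + 0.20 = 0.80 for the first and 0.20 + 0.60 = 0.80 for the second. The difference after the cut is exactly zero, although many ratings have moved from 4 to 5. In simulation with 20 independent ratings per condition, a rank test on five levels rejects in 48% of runs and Fisher's test on the cut in about 1%. For Fisher's test the figure is 1–2% at 12 to 30 per condition.

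**3. Power in a paired comparison.** Latent normal ratings were cut into five levels, with a shift of 0.7 SD, within-athlete correlation 0.4 and a two-sided 5% level. The McNemar z statistic on the cut rating was set against the Wilcoxon signed-rank z statistic on the five levels, for one pair of interventions and 20 athletes.

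| Satisfied in reference condition | After cut | Five levels |
|---|---|---|
| 50% | 45% | 67% |
| 79% | 27% | 57% |
| 88% | 12% | 51% |

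Type I error was 3–5% for both, so the gain is not bought with false positives. The five-level figures depend somewhat on how the levels are spaced: other spacings gave 56–60% in the second row and 45–51% in the third. In this setting, 60/79/87% of within-athlete pairs tie after the cut, against 31/47/58% on five levels.

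**4. The same comparison with a larger effect.** With a reference of .10/.20/.40/.20/.10 (30% satisfied), the same correlation and 20 athletes, the dichotomised rating has about 89% power at a shift of 1.2 SD and 98% at 1.5 SD. The five-level rating has 98% and 100%. Ties after the cut fall to 48% and 43%.

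**The case against.** The strongest defence is that the cut is a legitimate and readable choice. It is fixed in advance, sits at the natural verbal boundary and is not driven by the data. A proportion satisfied is easy to understand, and the Outcomes and Statistical Analysis sections agree with each other. Satisfaction is the last of the secondary outcomes, no power rests on it, and the Specific Objectives name performance and biochemical markers only. All of this stands, and it sets the weight of the point. It does not restore the lost power, and readability survives if the proportion is still reported.

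A reader might infer that the cut throws away most of the information in the rating. The documents do not support that, because they give no rating distribution. The efficiency loss is below half in four of the five distributions tried and exceeds half only near a ceiling. The idea that athletes would mostly answer 4 or 5 is itself an assumption, and one of the four conditions is lying at rest.

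A reader might also infer that the cut leaves little ability to separate the interventions even when athletes clearly prefer one. Step 4 shows otherwise for a large effect with a reference condition well away from the ceiling.

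Finally, Fisher's test treats four ratings from one athlete as independent, which is a separate and more serious fault on this endpoint. Correcting it with McNemar's test or Cochran's Q would leave the loss described here in place, since the dichotomised analysis in step 3 is already paired.

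**Conclusion.** The point holds as a matter of efficiency. The only analysis described for satisfaction uses a two-level version of a five-level rating. Wherever a real shift was simulated, the two-level version had less power, and it cannot see a difference confined to one side of the cut. The loss is moderate for spread or moderately positive ratings and severe only close to the ceiling.

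These figures illustrate the cost of the cut and do not predict this trial's power. The sample size is unknown, the paired figures are for a single comparison before any multiplicity adjustment, and they use McNemar's test where the protocol plans Fisher's. The choice is not a contradiction and introduces no bias. The jump comparison and its sample size are untouched.

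**What to change.** In the Outcomes section, make the five-point rating the analysed satisfaction endpoint. In the Statistical Analysis section, replace Fisher's exact test for this outcome with a within-athlete ordinal analysis: a Friedman test across the four interventions, followed by paired Wilcoxon signed-rank tests with Bonferroni adjustment (six pairs, so 0.05 / 6 ≈ 0.0083 each). Report the proportion satisfied or very satisfied for each intervention as a descriptive figure, ideally beside the full five-level distribution.

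The cost is one or two sentences. All five levels are already collected, so no data, visits or athlete burden are added. The small downside is that a rank-based result is less directly readable than a difference in proportions. The same change also replaces an unpaired test with one that respects the crossover.

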**Statistical Analysis**

To the best of our knowledge, no prior study will have compared PBMT-sMF, IPC, ESWT, and passive recovery in Cross Training athletes. Therefore, sample size will be calculated based on CMJ performance data from the first session, following a previously described method (Pinto et al., 2022). This calculation will be conducted by a blinded researcher and will use percentage changes in CMJ at 1-hour post-WOD (primary outcome). An 80% statistical power (α = 0.05; ANOVA) will be considered, and the WebPower (https://webpower.psychstat.org/models/means03/effectsize.php) and Statistics Kingdom (https://www.statskingdom.com/sample_size_regression.html) tools will be used for the computation.

Statistical analyses will follow the intention-to-treat principle (Elkins, 2015). The statistician will remain blinded to allocation to minimize bias. Data normality will be assessed using the Shapiro–Wilk test. Differences between interventions will be evaluated using repeated-measures ANOVA with Bonferroni post hoc tests. Both absolute values and percentage changes from baseline will be analyzed. Results will be presented as mean ± SD (tables) and mean ± SEM (figures). Fisher’s exact test will be used to compare satisfaction proportions across interventions. Statistical significance will be set at p < 0.05.

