**Participants**

The trial will be conducted in São José dos Campos, Brazil. Healthy male amateur Cross Training athletes aged between 18 and 35 years, who have been training at least four times per week for a minimum of one year, will be included. Exclusion criteria will include pharmacological use or recent musculoskeletal injuries. In addition, individuals who sustain musculoskeletal or joint injuries during the study will also be excluded.

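### The named repeated-measures ANOVA has no period term in a four-session Latin-square crossover, so any session drift costs power and, if sequences end up uneven, shifts the intervention contrasts

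*Protocol*

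**What the plan says.** The Blinding and Randomization section lists four cyclic sequences, the first being "Sequence 1: PR → PBMT-sMF → ESWT → IPC". Together they form a Latin square, so each intervention falls once in each session. On allocation it says: "Intervention sequences will be randomized (1:1:1:1) via www.randomization.org". It mentions no blocking.

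Study Sessions and Exercise Protocol adds: "The trial will comprise four sessions with seven-day washouts" and "Procedures will remain identical except for the randomized intervention applied". Assessments take place before and after each WOD.

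Under Outcomes, the primary outcome is the change in the functional test at 1 hour. Statistical Analysis names the comparison: "Differences between interventions will be evaluated using repeated-measures ANOVA with Bonferroni post hoc tests". It applies this to absolute values as well as percentage changes from baseline. Neither period, session nor sequence is named as a model term anywhere in the protocol.

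The Participants section provides one route to unequal sequences: "individuals who sustain musculoskeletal or joint injuries during the study will also be excluded". No replacement rule is given.

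**The concern.** A Latin square lets session effects be separated from intervention effects, but only if the analysis uses that structure. A repeated-measures ANOVA with intervention as its only within-athlete factor does not. Athletes do the same maximal workout and jump test four times at weekly intervals, so some adaptation to the bout is possible. Such drift would have two consequences:

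- **Sequences equal:** the contrasts stay unbiased, but period variation is counted as residual error. The F test becomes conservative and loses power.
- **Sequences unequal:** interventions have different average session numbers, so part of the drift appears as a difference between interventions.

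The stated aim is to compare the therapies with one another, so the pairwise contrasts are the results that readers will use.

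**Working it through.** The protocol gives no sample size, SD, effect or drift, so it has no figure to reproduce. The check uses its four sequences with labelled assumptions.

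**Assumptions.** Residual within-athlete SD is 1. Drift is linear, totalling D (in SDs) from session 1 to session 4, and acts on the analysed variable. N = 20. For power, one intervention is better by 0.75 SD. Alpha is 0.05, as in the protocol.

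**Error term, balanced sequences (5/5/5/5).** The centred period effects are D × (−1/2, −1/6, 1/6, 1/2), and their squares sum to 0.556 D². Without a period term:

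E(MSE) = 1 + N × 0.556 D² / [3(N − 1)] = 1 + 20 × 0.556 D² / 57 = 1 + 0.195 D²

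This gives 1.05, 1.19 and 1.78 for D = 0.5, 1 and 2. Simulation gave 1.04, 1.19 and 1.77. With period in the model the MSE stays at 1.00.

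**Power, balanced sequences.** The noncentrality with period in the model is 20 × 0.75² × 3/4 = 8.44. On 3 and 54 degrees of freedom this gives about 65% power, whatever the drift. Simulated comparison:

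| Drift D | Power without period | Power with period | Loss (points) |
|---|---|---|---|
| 0.25 SD | 64–65% | 64–65% | about 0–1 |
| 0.5 SD | 62% | 64–65% | about 1–3 across runs |
| 1 SD | 54% | 64–65% | about 11 |
| 2 SD (extreme) | 28% | 64–66% | about 37 |

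Without period, type I error is about 2.6% at 1 SD and 0.3–0.4% at 2 SD. With period it is about 5%.

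**Bias, uneven sequences (8/5/4/3 for sequences 1 to 4).** Mean session number by intervention:

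- PR: (8×1 + 5×4 + 4×3 + 3×2)/20 = 2.3
- PBMT-sMF: (8×2 + 5×1 + 4×4 + 3×3)/20 = 2.3
- ESWT: (8×3 + 5×2 + 4×1 + 3×4)/20 = 2.5
- IPC: (8×4 + 5×3 + 4×2 + 3×1)/20 = 2.9

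Bias against PR is the difference in mean session × D/3. At D = 1 it is 0.00 for PBMT-sMF, 0.2/3 = 0.07 SD for ESWT and 0.6/3 = 0.20 SD for IPC. Overall type I error for this split was 4.8% at 1 SD and 3.8% at 2 SD. In the other uneven splits tried, at N = 12 and 16, it reached at most about 5.6%. With period in the model the bias is zero in every split tried.

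**How uneven might the counts be?** This depends on a further assumption. If the list were generated by simple randomisation, about 69% of lists of 20 would have a gap of 4 or more between the largest and smallest sequence, and about 1% would be exactly balanced. If the list is blocked, only dropout and exclusions create imbalance.

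**The case against.** **The primary outcome is a change score.** With assessments before and after each WOD, the natural reading is a separate baseline in each session. An additive shift in jump height, such as learning the test, then cancels from the change and largely from the percentage change. This stands, and it narrows the point. What remains for the primary outcome is drift in how far the WOD depresses the jump at 1 hour. Absolute values have no such protection.

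**No drift is documented.** Participants have trained at least four times a week for at least a year, time of day is fixed, and activity around each session is restricted. A reader might infer that sizeable learning across sessions is to be expected. The protocol supports only that drift is possible. At 0.5 SD or less the loss with balanced sequences is small, and 2 SD in a change score is extreme.

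**Imbalance is not established.** A reader might infer simple randomisation from the lack of any mention of blocking. The text says neither, and block details are often kept out of protocols. Any bias from chance imbalance also has no systematic direction: it depends on which sequence is over-represented, and 0.20 SD is the worst pair against PR in the example.

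**An SAP might add the term.** It might. But the protocol names the method and describes it as a comparison of interventions, so this is a stated choice that needs correcting rather than a detail left open.

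**Conclusion.** The point holds in limited form. As worded, the analysis leaves out the period factor that the Latin square allows it to remove. With balanced sequences the consequence is a conservative test. Under the assumed 20 athletes and 0.75-SD effect, the power loss is negligible to modest for drift up to 0.5 SD and about 11 points at 1 SD. With unequal sequences, contrasts move by a fraction of the drift, up to 0.20 SD against PR in the 8/5/4/3 example at 1 SD.

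Two stronger readings are not supported. One is that the plan produces false positives: overall type I error stayed near or below 5% in the settings tried. The other is that the primary comparison will be biased: that needs both uneven sequences and drift in the response to the WOD, and the protocol establishes neither. The case for change rests on a cheap correction to a named method, not on a demonstrated large error.

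**What to change.** Add period (session 1 to 4) as a fixed effect in the primary analysis of 1-hour CMJ change. Use either a crossover ANOVA, or a linear mixed model with intervention and period fixed and participant random. Take the Bonferroni-adjusted pairwise contrasts from that model, and use the same model for the absolute values.

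The cost is a change of analysis wording and 3 degrees of freedom. With no drift at all, the power given up is under 1 point if sequences are balanced and about 2 points with an 8/5/4/3 split.

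Optionally, if this is not already done, generate the sequence list in blocks of four. That is a small change to the randomisation procedure as well as to the text. It limits chance imbalance but does not replace the period term, because exclusions can still unbalance the sequences.

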**Objectives**

**General Objective:**

To compare the effects of three different therapeutic resources—PBMT-sMF, IPC, and ESWT—on muscle recovery in Cross Training participants.

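### Single-step Bonferroni is valid for the six pairwise comparisons, but Holm's step-down version gives modestly more power at the same 5% familywise error

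*Protocol*

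**What the plan says.** The Statistical Analysis section of the protocol fixes the test and the correction: "Differences between interventions will be evaluated using repeated-measures ANOVA with Bonferroni post hoc tests". The level follows in the same section: "Statistical significance will be set at p < 0.05". No step-down version is named, and no reason is given for the single-step one.

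The design is fully within-participant: "Each participant will complete all four interventions across weekly sessions with seven-day washout periods". The primary outcome is a single time point: "The primary outcome will be the change in performance on the functional test, assessed 1-hour post-WOD". The General Objective is comparative ("To compare the effects of three different therapeutic resources"), and the end of the Background says the aim is to identify the modality best suited to recovery in this sport.

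Power is planned for the overall test only: "An 80% statistical power (α = 0.05; ANOVA) will be considered". No sample size, SD or effect is stated, because "sample size will be calculated based on CMJ performance data from the first session".

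**The concern.** A significant ANOVA says only that the four conditions are not all equal. The stated objective is answered by the pairwise tests, and several pairs may have to be separated to rank the modalities. Bonferroni holds every pair to the strictest threshold, even after some pairs have been rejected and fewer true null hypotheses can remain. Holm relaxes the threshold at each rejection and keeps the same error guarantee.

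At stake is some power on the second and later differences, in a trial whose pairwise tests are not separately powered. The validity of the conclusions is not in question.

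**Working it through.** **Inputs from the protocol.** Four conditions, each participant receiving all of them (Blinding and Randomization); α = 0.05 and 80% ANOVA power (Statistical Analysis); primary outcome at 1 hour (Outcomes). The protocol gives no pairwise power figure to reproduce.

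**Assumptions.** n = 12 to 24; two-sided tests; independent normal errors; no period or carryover effect. Effects d are in units of the SD of the paired difference, so the residual variance is 0.5.

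**Step 1: number of pairs.** C(4,2) = 4 × 3 / 2 = 6. The protocol does not state this number; it follows from the four conditions.

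**Step 2: thresholds.**
- Bonferroni: 0.05/6 = 0.00833 for all six.
- Holm, on the ordered p-values: 0.05/6, 0.05/5, 0.05/4, 0.05/3, 0.05/2, 0.05/1 = 0.00833, 0.0100, 0.0125, 0.0167, 0.0250, 0.0500, stopping at the first non-rejection.

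No Holm threshold is below 0.00833, so Holm rejects every pair that Bonferroni rejects. The first step is identical, so both methods make at least one rejection in exactly the same trials. These two facts do not depend on simulation.

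**Step 3: effects that match the planned power.** The ANOVA noncentrality is λ = n Σ(μᵢ − μ̄)² / 0.5, with 3 and 3(n − 1) degrees of freedom. For n = 24:
- two conditions against two: λ = 2nd²; d = 0.490 gives 2 × 24 × 0.490² = 11.5
- three against one: λ = 1.5nd²; d = 0.566 gives 1.5 × 24 × 0.566² = 11.5
- equally spaced, d from lowest to highest: λ = (10/9)nd²; d = 0.658 gives (10/9) × 24 × 0.658² = 11.5

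Each gives 80% ANOVA power.

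**Step 4: simulated power, Bonferroni to Holm** (40,000 trials, n = 24, t tests on the pooled error).

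| Pattern | Average per true pair | All true differences | At least one true difference |
| --- | --- | --- | --- |
| Two against two | 38.4% to 42.2% | 9.8% to 15.8% | 71.6% to 71.6% |
| Three against one | 52.5% to 55.4% | 27.9% to 33.9% | 76.5% to 76.5% |
| Equally spaced | 24.1% to 26.3% | 0% to 0% | 75.9% to 75.9% |

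At n = 16 the pooled results are almost the same: 38.6% to 42.5%, 52.7% to 55.8% and 24.2% to 26.5% per pair. With separate paired t tests at n = 16, the levels are lower but the gains similar:
- two against two: 31.8% to 35.3% per pair, 4.8% to 9.8% for all differences
- three against one: 44.2% to 47.4% per pair, 18.6% to 24.3% for all differences
- equally spaced: 20.4% to 22.5% per pair

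**Step 5: familywise error.** With no true differences, both methods give about 4%. When some differences are real and some pairs are truly equal, Bonferroni runs at about 1.6% to 2.4% and Holm at about 2.4% to 4.1%. Holm stays below 5% in every case.

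**The case against.** The strongest reply is that nothing here is wrong. Bonferroni is a recognised correction, it is consistent with the stated significance level, and preferring a somewhat more powerful procedure is a matter of choice. That stands in part: this is a loss of efficiency, not an error or a contradiction. It remains worth raising because the protocol names the single-step method explicitly, and an alternative with the same guarantee never rejects less.

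A second reply concerns intervals. Bonferroni intervals agree with Bonferroni tests, and Holm has no equally simple counterpart. This is a real but small cost, since the protocol plans only means with SD or SEM and mentions no simultaneous intervals.

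Three stronger readings are tempting and are not supported:
- *The gain is large.* With d = 0.8, two against two and n = 16, power for all four true differences rises from about 35% to 47%. But λ = 2 × 16 × 0.8² = 20.5 there, which is about 97% ANOVA power. At the planned 80% the gain is about half that, and even with Holm the chance of finding every true difference is about 34% at best in the patterns above.
- *Holm would let the trial rank all the modalities.* A full ranking implies graded effects. With equally spaced effects at the planned power, the chance of separating every pair is essentially zero under both methods.
- *Bonferroni always runs far below 5%.* That is so only when some differences are real; under the global null it runs at about 4%, the same as Holm.

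**Conclusion.** A cheap improvement, not a defect that threatens the trial. The dominance of Holm over Bonferroni is a mathematical result and needs no assumption about this trial. The size of the gain does rest on assumptions, because the protocol states no sample size, SD or effect. With n = 12 to 24, the ANOVA at 80% power and no carryover, it is about 2 to 4 points of average power per true pair. For finding all true differences it is about 6 points (5 to 6 across pooled and paired tests) with two effect levels, and nil with equally spaced effects. The chance of finding at least one difference does not improve. If the post hoc family also spans time points, it has more than six members; the advantage keeps its direction, but its size was not calculated for that case.

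**What to change.** In the Statistical Analysis section, replace the Bonferroni wording, for countermovement jump at 1 hour, with: *all six pairwise comparisons with Holm-adjusted p-values (familywise error 5%)*. Make the change before the outcome data are analysed by intervention.

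The change needs no extra participants, data or assumptions, and the method is available in standard software. If confidence intervals are reported, for example Bonferroni intervals, state that they are not derived from the Holm procedure and may not always agree with its decisions: a pair that Holm rejects can have a Bonferroni interval that includes zero.
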